### Primary Efficacy Endpoint

For body mass index (BMI) and weight, descriptive statistics will be presented at baseline and at 24 weeks. The change from baseline to 24 weeks will be analyzed using a Paired t-test or Wilcoxon signed rank test.

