## Rationale

This study is a large-scale, prospective, multicenter, non-interventional database observational study aimed at observing the weight loss effects, efficacy, and safety of Envlo Tab./Envlomet SR Tab. in patients with Type 2 diabetes over 24 weeks.

As a single-arm observational study, the number of subjects was calculated using G*Power 3.1.9.7, referencing the mean and standard deviation of the changes in weight and body mass index (BMI) from baseline to 12 or 24 weeks from previous Phase 2 and Phase 3 clinical studies (Figure 2) ^20)^

[Assumptions]

- Effect size: 0.25 (Mean of difference 2.5, SD of difference 10.0)
- Power: 0.95
- α error: 0.05
- Drop-out rate: 30%

[figure not shown]

Figure 2. Sample Size Calculation (G*Power)

Based on previous studies, assuming an average weight change of 2.5 kg and a standard deviation of 10.0 for the intervention with Envlo Tab. or Envlomet SR Tab., the effect size is 0.25. Setting the power: 0.95, α error: 0.05, the total required sample size is estimated to be approximately 210 subjects. Considering a drop-out rate of about 15%, we plan to recruit around 240 subjects.

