## Completion and Withdrawal/Dropout of Observational Study

1. **Completion and Termination of Observational Study**

A subject is considered to have completed the observational study upon completing the close-out visit procedures at the 24-week point after their first visit (baseline) and the investigational product administration. This observational study is deemed complete when the last subject finishes their observational study participation.

1. **Withdrawal/Dropout of Observational Study**

Subjects can discontinue their participation in the study at any time at their discretion. The investigator or sponsor can also withdraw or drop a subject’s participation at any time for safety, behavioral, or administrative reasons. If a subject is withdrawn/dropped due to an AE, every effort should be made to follow the course of the AE in the subject. The following are conditions under which a subject might be withdrawn/dropped from the study, and the investigator shall enter the collected study data into the eCRF up to the point of withdrawal/dropout:

A subject may be withdrawn or dropped from the observational study if:

1. A subject not meeting the inclusion/exclusion criteria was discovered during the observational study
2. Adverse Event(AE)

: If the investigator determines that it is difficult to continue the observational study due to an adverse event

1. Withdrawal by Subject (or his/her legal representative)
2. Non-Compliance with Investigational Product

: Subjects do not agree to or follow the investigator’s instructions related to the investigational product.

1. Lost to Follow-Up

: Subjects cannot be contacted for follow-up

1. Physician Decision

If a subject is withdrawn/dropped, the investigator must notify the sponsor and make every effort to complete the end-of-observation study evaluation. The reasons for dropout will be recorded in the electronic-case report form (eCRF) and the subject’s source document. Any withdrawn subject cannot participate in the same study again.

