# Method of Observational Study

## Overall Design of Observational Study

This observational study is designed as a prospective, multicenter observational study to confirm the weight loss efficacy and safety of Envlo Tab. or Envlomet SR Tab. over 24 weeks in patients with Type 2 Diabetes in real-world primary care settings.

The study plans to recruit patients with Type 2 Diabetes who are scheduled to receive Envlo Tab. or Envlomet SR Tab. based on the medical judgment of the investigator (responsible physician) and in accordance with the approved indications (effectiveness ∙ effect, administration∙ and dosage, precautions for use, etc.) in real-world clinical settings.

Regardless of whether they are currently undergoing pharmacotherapy for diabetes, all eligible patients who are considered suitable for Envlo Tab./Envlomet SR Tab. can be enrolled in this study. However, despite the decision to administer Envlo Tab./Envlomet SR Tab., observation is only possible with the subject's voluntary consent to participate in the study as determined by the investigator's medical judgment.

This observational study will collect demographic information, physical measurement, vital signs, and other relevant information up to 24 weeks after the administration of Envlo Tab./Envlomet SR Tab. in real-world clinical settings, irrespective of whether the medication is administered or not. Data will be collected based on medical records documented in real-world clinical settings. There are no mandatory visits, tests, or treatments specifically required by this observational study.

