### Efficacy Analysis Set

Subjects who meet the inclusion/exclusion criteria, have been enrolled in this study, received the investigational product at least once, and have had their weight measured post-baseline will be included in the efficacy analysis set.

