### Safety Analysis Set

Subjects who meet the inclusion/exclusion criteria, have been enrolled in this study, received the investigational product at least once according to the approved indications, and have undergone safety evaluations will be included in the safety analysis set.

1. **Methods of Analysis**
2. **General Principles**

Continuous variables will be presented as descriptive statistics (number of subjects, mean, standard deviation, median, minimum, maximum), and categorical variables will be presented as frequencies and percentages. Unless otherwise specified, all tests will be two-sided with a significance level of 5%. All p-values will be reported to a maximum of four decimal places. If not exactly divisible, values will be rounded to two decimal places, rounding up at the third decimal place.

1. **Demographic and Baseline Characteristics**

For the demographic data (age, gender, etc.) and baseline characteristics of the study subjects, continuous variables will be presented as mean, standard deviation, median, minimum, and maximum values, while categorical variables will be presented as frequency and percentage.

1. **Efficacy Endpoints**

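### Section 3.5 lets observation end for non-compliance or an adverse event, against section 4.1, and the paired week-24 test omits subjects weighed only at week 12, so weight loss may be overstated by an unknown amount

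*Protocol*

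**What the plan says.** **Follow-up.** Section 4.1 (Overall Design), and the design row of the synopsis in the same terms, undertake to gather information for 24 weeks after the drug is started, "irrespective of whether the medication is administered or not".

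**Withdrawal.** Section 3.5 lists grounds on which a subject may be withdrawn from the study. They include "Non-Compliance with Investigational Product", and an adverse event where the investigator judges that staying in the study is difficult. In these cases "the investigator shall enter the collected study data into the eCRF up to the point of withdrawal/dropout". The section also asks the investigator to try to obtain a closing evaluation, but does not say when it should fall.

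**Analysis set.** Under section 8.2, eligible subjects who took at least one dose and "have had their weight measured post-baseline will be included in the efficacy analysis set". No visit is named, so a week-12 weight is enough.

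**Primary test.** For BMI and weight, section 8.2 states: "The change from baseline to 24 weeks will be analyzed using a Paired t-test or Wilcoxon signed rank test".

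**The concern.** There are two linked problems.

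First, a subject who stops or does not follow the product is kept under observation by section 4.1 but may be removed under section 3.5. The twelve sites could settle this differently. A statistical analysis plan cannot repair it afterwards, because weights that were never recorded cannot be recovered by analysis.

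Second, the analysis set and the named test do not match. The set admits a subject weighed only at week 12, but a paired comparison of baseline with week 24 has no place for that subject.

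Two of the withdrawal grounds, non-compliance and adverse events, are plausibly related to how much weight a subject loses. Losing such subjects would shift the estimate towards people who took and tolerated the drug. The study has a single arm, so no control group carries a similar shift to offset it. The stated aim (section 2) is the effect in a real-world setting, and weights after the drug is stopped belong to that question.

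**Working it through.** **1. The plan's own figure.** Section 3.2 assumes a mean change of 2.5 kg with SD 10.0 kg, so d = 2.5/10.0 = 0.25, with power 0.95 and alpha 0.05; section 8.2 makes tests two-sided. For a paired t-test with noncentrality 0.25 × √n and n − 1 degrees of freedom, the smallest n with power of at least 0.95 is 210 (power 0.9501). The normal approximation, ((1.960 + 1.645)/0.25)², gives 208. The stated figure of about 210 is reproduced.

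Section 3.2 then raises recruitment to about 240 to cover drop-out. That is consistent with drop-outs not counting in the test. Recruiting more subjects restores precision but does not change which subjects are averaged.

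**2. Who enters the test as written.**

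| Subject | Efficacy Analysis Set | Paired week-24 test |
|---|---|---|
| Stops the drug, stays in the study, weighed at week 24 | yes | yes |
| Withdrawn after a week-12 weight, none at week 24 | yes | no |
| Withdrawn before any post-baseline weight | no | no |
| Withdrawn, with a weight at an early closing evaluation | yes | not stated |

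**3. How large the effect could be.** Let C be the mean loss in completers (those with a week-24 weight), D the mean loss at week 24 that drop-outs would have shown, and p the drop-out proportion.

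- Mean over all treated subjects: M = (1 − p) × C + p × D
- Overstatement by the completer mean: C − M = p × (C − D)

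C = 2.5 kg is taken from section 3.2. Both p = 15% and p = 30% appear in section 3.2; they conflict, which is a separate matter, and here they serve as a range. D is not in the protocol and is an **assumption**.

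| D (assumed) | M at 15% | Overstatement at 15% | M at 30% | Overstatement at 30% |
|---|---|---|---|---|
| 0 kg | 2.125 kg | 0.375 kg (17.6%) | 1.75 kg | 0.75 kg (42.9%) |
| 1.0 kg | 2.275 kg | 0.225 kg (9.9%) | 2.05 kg | 0.45 kg (22.0%) |
| 2.5 kg | 2.5 kg | 0 | 2.5 kg | 0 |
| 3.0 kg | 2.575 kg | −0.075 kg (−2.9%) | 2.65 kg | −0.15 kg (−5.7%) |

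Example: 0.85 × 2.5 + 0.15 × 0 = 2.125, and (2.5 − 2.125)/2.125 = 17.6%.

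**The case against.** The strongest reply has four parts.

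- **Withdrawal is discretionary.** Section 3.5 permits it and does not require it, and stopping the drug does not trigger it. Section 4.4 already records discontinuation and its reason at each visit. A subject who stops but stays in the study counts in the primary test. Section 3.5 also lists grounds that need not relate to the drug, such as ineligibility and loss to follow-up. All of this stands, and it limits how many subjects are affected. It does not remove the conflict with section 4.1.
- **A closing evaluation is sought.** It would be wrong to read section 3.5 as simply cutting off data. But the evaluation is best-effort and untied to week 24, and the protocol does not say whether such a weight enters the week-24 test.
- **Missing-data rules may sit in a statistical analysis plan that is not shown.** Their absence here is no finding. What remains is that the test the protocol does name cannot use some of the subjects its analysis set admits, and that no later document can supply weights that were not collected.
- **A paired test is conventional for a single-arm study and matches the sample size calculation.** True, and it is not an error in itself. With complete data, a repeated-measures model with unstructured covariance gives the same mean change, so nothing is lost by using it.

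A reader might infer that the protocol restricts the primary analysis to adherent completers and that the weight loss will be overstated, by 18% or 43%. The documents do not support that. No sentence limits the test to completers; the limit follows from the paired form. Those percentages hold only if drop-outs lose exactly 0 kg, and the last rows of the table show that the bias can vanish or reverse.

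**Conclusion.** The point holds in a limited form. Sections 3.5 and 4.1 disagree on whether observation continues when the product is not taken. As written, the primary test also leaves out efficacy-set subjects who have no week-24 weight. Overstatement of the weight loss is the likelier direction, because non-compliance and intolerance are among the reasons for leaving, but it is possible and not proved. With completers at 2.5 kg, drop-outs assumed between 0 and 2.5 kg and drop-out of 15% to 30%, it ranges from 0 to 0.75 kg. This is an illustration, not an estimate. The point should be corrected, but it does not by itself invalidate the plan.

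**What to change.** 1. **Sections 3.5 and 4.1 (and the synopsis).** Reconcile them so that stopping or not following the product is distinguished from leaving the study. Keep recording routine-care weight to week 24 unless consent is withdrawn or the subject is lost. This concerns data collection only; decisions on treatment stay with the physician.
2. **Section 8.2.** Estimate the week-24 mean change, with a 95% confidence interval, from a repeated-measures mixed model (unstructured covariance) of baseline, week-12 and week-24 weight in the whole Efficacy Analysis Set, and likewise for BMI. Keep the paired test as a completer sensitivity analysis.
3. **State the limits.** The model assumes that weights are missing at random given those observed. If drop-outs resemble completers at week 12 and diverge later, it will not correct the bias. It does not cover subjects with no post-baseline weight, so report their number and reasons for leaving.

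**Cost.** The wording changes need an IRB-approved amendment, and there is slightly more analysis work. No visits are added, since data come from routine care. The reported mean loss may be less favourable. The change to 3.5 helps only subjects not yet withdrawn, so it should come early.

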### Secondary Efficacy Endpoints

For each secondary efficacy evaluation variable, descriptive statistics will be presented at baseline, 12 weeks, and 24 weeks. The change from baseline to 12 weeks or 24 weeks will be analyzed using a Paired t-test or Wilcoxon signed rank test.

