| **Statistical Analysis Method** | **General Principles**  Continuous variables will be presented as descriptive statistics (number of subjects, mean, standard deviation, median, minimum, maximum), and categorical variables will be presented as frequencies and percentages. Unless otherwise specified, all tests will be two-sided with a significance level of 5%. All p-values will be reported to a maximum of four decimal places. If not exactly divisible, values will be rounded to two decimal places, rounding up at the third decimal place.  **Efficacy Endpoints**  For primary and secondary efficacy endpoints, descriptive statistics will be presented at baseline, 12 weeks, and 24 weeks. Changes from baseline at 24 weeks or 12 weeks will be analyzed using the Paired t-test or Wilcoxon signed rank test.  **Exploratory Endpoints**  Descriptive statistics will be presented for exploratory endpoints at baseline, 12 weeks, and 24 weeks. Changes from baseline at 24 weeks or 12 weeks will be analyzed using the Paired t-test or Wilcoxon signed rank test.  **Safety Endpoints**  For adverse events (AEs),∙adverse drug reactions (ADRs), serious adverse events (SAEs),∙serious adverse drug reactions (SADRs), unexpected adverse events∙, unexpected adverse events,∙collected during the study period, the number of subjects with events, the number of events, incidence rates, and two-sided 95% confidence intervals will be presented. The severity of the adverse events, the causal relationship with the investigational product, actions taken concerning the investigational product, other actions taken, and the outcomes of the adverse events will be summarized.  Descriptive statistics for vital signs will be presented at baseline, 12 weeks, and 24 weeks. Changes from baseline at 24 weeks will be analyzed using the Paired t-test or Wilcoxon signed rank test. Descriptive statistics for laboratory tests will be presented at baseline, 12 weeks, and 24 weeks. Changes from baseline at 24 weeks will be analyzed using the Paired t-test or Wilcoxon signed rank test.  Additionally, the frequency and percentage of normal (Normal or NCS) and clinically significant abnormal (CS) changes will be summarized. Detailed information on subjects with clinically significant abnormal (CS) items will also be listed. |

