# Evaluation Criteria and Methods, and Statistical Analysis Methods

## Endpoints

1. **Efficacy Endpoints**
2. **Primary Efficacy Endpoint**

- Change in BMI and weight at 24 weeks compared to baseline

1. **Secondary Efficacy Endpoints**
2. Change in BMI and weight at 12 weeks compared to baseline
3. Proportion of subjects achieving ≥ 5% reduction in BMI and weight at 12 and 24 weeks compared to baseline
4. Change in body composition analyzer indicators (body fat mass, visceral fat mass, muscle mass, waist/hip circumference, etc.) at 12 and 24 weeks compared to baseline
5. Change in HbA1c at 12 and 24 weeks compared to baseline
6. Change in FPG at 12 and 24 weeks compared to baseline
7. Proportion of subjects achieving HbA1c < 7% at 12 and 24 weeks compared to baseline
8. Proportion of subjects achieving HbA1c < 6.5% at 12 and 24 weeks compared to baseline
9. Proportion of subjects achieving therapeutic response [change in HbA1c (baseline HbA1c – HbA1c at each evaluation time point) > 0.5% or HbA1c < 7%] at 12 and 24 weeks compared to baseline
10. **Exploratory Endpoints**
11. Change in lipid levels (total cholesterol, LDL-C, HDL-C, triglycerides) at 12 and 24 weeks compared to baseline
12. Change in liver function markers (AST, ALT, γ-GTP) at 12 and 24 weeks compared to baseline
13. Change in renal function markers (e-CFR, UACR (Urine Albumin to Creatinine Ratio), UGCR (Urine Glucose to Creatinine Ratio)) at 12 and 24 weeks compared to baseline
14. Change in other body composition analyzer indicators (body water, intracellular water, extracellular water, extracellular water ratio, abdominal fat percentage, etc.) at 12 and 24 weeks compared to baseline
15. **Safety Endpoints**
16. Definition of an adverse drug reaction (ADR)
17. Incidence rate and number of occurrences of Serious ADRs (SADRs)
18. Adverse events of Special Interest^*^

* Hypoglycemia, urinary tract infection, genital infection, frequent urination, polyuria

1. Laboratory tests, vital signs, physical examination results

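### The secondary-endpoint test rule does not exempt the proportions, so as written the ≥5% reduction endpoint is tested against a baseline that is zero for every subject

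*Protocol*

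**What the plan says.** Protocol Section 8.2, Secondary Efficacy Endpoints, has two sentences. The first sets the scope: "For each secondary efficacy evaluation variable, descriptive statistics will be presented at baseline, 12 weeks, and 24 weeks". The second names the test: "The change from baseline to 12 weeks or 24 weeks will be analyzed using a Paired t-test or Wilcoxon signed rank test". No other test is named for secondary endpoints.

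The synopsis (Statistical Analysis Method) treats primary and secondary endpoints together: "For primary and secondary efficacy endpoints, descriptive statistics will be presented at baseline, 12 weeks, and 24 weeks", followed by "Changes from baseline at 24 weeks or 12 weeks will be analyzed using the Paired t-test or Wilcoxon signed rank test".

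Section 8.1 lists four secondary endpoints that are proportions:

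- "Proportion of subjects achieving ≥ 5% reduction in BMI and weight at 12 and 24 weeks compared to baseline"
- "Proportion of subjects achieving HbA1c < 7% at 12 and 24 weeks compared to baseline"
- "Proportion of subjects achieving HbA1c < 6.5% at 12 and 24 weeks compared to baseline"
- "Proportion of subjects achieving therapeutic response [change in HbA1c (baseline HbA1c – HbA1c at each evaluation time point) > 0.5% or HbA1c < 7" (the limit being 7%), at the same two time points.

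All four are worded as comparisons with baseline. The General Principles in Section 8.2 say that categorical variables are shown as frequencies and percentages. That governs display and says nothing about testing.

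**The concern.** A paired test of change needs a baseline value that could have differed from the follow-up value in either direction. A fall of at least 5% is measured from baseline, so its indicator is 0 for every subject on Day 0 and no paired difference can be negative. The null hypothesis becomes that nobody ever loses 5%, which a handful of subjects will overturn whatever the drug does.

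This endpoint is the responder form of the primary outcome in a single-arm weight-loss study, so a p-value attached to it is likely to be quoted. A reader could take it as evidence of a worthwhile response rate when it shows only that some subjects lost 5%.

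**Working it through.** **Inputs.** Two-sided α = 0.05 (Section 8.2, General Principles). Effect size 0.25, power 0.95, about 210 subjects required, about 240 recruited, drop-out about 15% (Section 3.2).

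**The plan's own figure.** A paired t-test with effect size 2.5/10.0 = 0.25, two-sided α = 0.05 and power 0.95, by the noncentral t distribution, gives n = 210 (power 0.9501). The stated figure reproduces. Recruiting 240 and losing 15% leaves 240 × 0.85 = 204, so N = 204 to 210 is used below. Section 3.2 also lists a 30% drop-out rate, which would leave 240 × 0.70 = 168; this serves as a sensitivity value.

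**1. Reduction of at least 5%, paired t-test.** Let k of N subjects respond. The differences are k ones and N − k zeros, and the statistic reduces to t = √[k(N − 1)/(N − k)].

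| N | k | t | p |
|---|---|---|---|
| 210 | 3 | √(3 × 209/207) = 1.74 | 0.083 |
| 210 | 4 | √(4 × 209/206) = 2.01 | 0.045 |
| 204 | 4 | √(4 × 203/200) = 2.01 | 0.045 |

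The threshold is 4 responders: 4/210 = 1.9% or 4/204 = 2.0%. It is also 4 at N = 168 and at N = 240.

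**2. Reduction of at least 5%, Wilcoxon signed rank test.** Zero differences are dropped and the k remaining ones all have the same sign, so the exact two-sided p is 2 × 0.5^k.

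- k = 4: p = 0.125
- k = 5: p = 0.0625
- k = 6: p = 0.031

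The exact threshold is 6 responders: 6/210 = 2.9%, 6/204 = 2.9%. With the normal approximation, 4 responders suffice (p = 0.0455).

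**3. How likely is significance?** The protocol gives no expected responder rate, so these rates are assumptions. Binomial probabilities at N = 210:

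| Assumed true rate | P(at least 4) | P(at least 6) |
|---|---|---|
| 2% | 60.7% | 24.6% |
| 5% | 99.4% | 95.4% |
| 10% | above 99.99% | above 99.99% |

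**4. Therapeutic response.** At baseline the fall in HbA1c is zero, so the limb requiring a fall above 0.5% cannot be met. The HbA1c < 7% limb can be: Sections 3.3 and 3.4 set no HbA1c entry limit, and Section 4.1 admits patients already on diabetes drugs. A test of change would compare a two-limb definition at follow-up with a single limb at baseline.

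**5. HbA1c < 7% and < 6.5%.** Baseline status can be 0 or 1, so the pairing is genuine. If b subjects gain the target and c lose it, all b + c non-zero differences are tied in size. The signed rank statistic (tie-corrected normal form) is then z = (b − c)/√(b + c), which is McNemar's statistic. An assumed example with b = 40, c = 15, N = 210 gives z = 25/√55 = 3.37, p = 0.00075 by both tests; the paired t-test gives 0.00066.

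**6. What an interval would show instead.** Exact 95% CIs at N = 210, with illustrative counts: 4 responders, 1.9% (0.5 to 4.8%); 21 responders, 10% (6.3 to 14.9%); 42 responders, 20% (14.8 to 26.1%). The first and last are both significant under the stated rule, yet they describe very different results.

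**The case against.** The best reply is that the word each governs only the sentence on descriptive statistics. The test sentence has its own subject, the change from baseline, and Section 8.1 labels some endpoints as changes and others as proportions. On that reading the test serves the changes, and the General Principles cover the proportions. Nothing in the protocol expressly sends a 0/1 indicator into a t-test. This reading is possible, but it is not stated: the test sentence follows directly on one covering every secondary variable, the proportions are themselves worded against baseline, and the synopsis makes no exception either.

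Three stronger readings are tempting, and the protocol does not support them.

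- A reader might infer that therapeutic response is also zero for everyone at baseline. It is not, because its HbA1c < 7% limb can already be met.
- A reader might infer that the two HbA1c targets are given an invalid test. The Wilcoxon option is equivalent to McNemar's test on such data, so only the wording is at fault.
- A reader might infer that the proportions will not be reported. Frequencies and percentages are planned. Only an interval is unmentioned (Section 8.2 plans 95% CIs for adverse events but for no efficacy proportion), and a statistical analysis plan, not available here, may supply it. The missing interval is therefore not a fault in itself.

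It is also fair that these are secondary endpoints in a non-interventional study, and that no decision rule hangs on a responder p-value.

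**Conclusion.** The rule is wrong as written for the ≥5% reduction endpoint. Followed literally, it yields significance from 4 responders (about 2%) by paired t-test or 6 (about 3%) by exact Wilcoxon test, and is close to certain to do so at an assumed true rate of 5% or more. The thresholds rest on two-sided α = 0.05 and an all-zero baseline, and hardly depend on N. The chances of significance rest on assumed responder rates.

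For therapeutic response the fault is a mismatched pair, not an all-zero baseline. For the two HbA1c targets, naming the test is a clarification. Severity is minor to moderate: the primary analysis and the sample size do not change.

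**What to change.** In Section 8.2 and in the synopsis:

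- Limit the paired t-test or Wilcoxon rule to continuous endpoints.
- Report the ≥5% reduction and therapeutic response at weeks 12 and 24 as n, % and an exact or Wilson 95% CI, with no test against baseline.
- Beside therapeutic response, show how many subjects already had HbA1c < 7% at baseline, so that those who merely stayed below 7% are visible.
- For HbA1c < 7% and < 6.5%, name McNemar's test with a 95% CI for the change in proportion.

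The cost is a few sentences and trivial programming, with no change to data collection, visits or sample size. It should be settled before database lock.
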